## Abstract

**Background/aims:**

Borderline personality disorder (BPD) is a severe mental disorder characterized by an unstable sense of self, intense and rapidly changing affect, as well as impulsive and self-destructive behaviors. Interpersonal relationships of individuals with BPD are characterized by marked instability, a lack of dependability, and quick changes between love and hate. For children of individuals with BPD, this can lead to permanent stress and attachment insecurity and an increased risk of adverse physical and mental health development. To reduce dysfunctional parenting and improve positive parenting, and in turn, to promote healthy child development, a group intervention for mothers with BPD was developed. This study aims to evaluate this first disorder-specific parenting intervention for BPD in a randomized controlled trial.

**Method:**

In a parallel-group, two-arm, randomized controlled trial, an initial *N* = 178 mothers diagnosed with BPD and their children aged 6 months to 6 years are assigned to either the parenting intervention or a waiting control group. If taking place, participants of both groups continue their regular treatment for BPD diagnosis (e.g., individual therapy, medication). The primary outcomes are changes in parenting from baseline (day 0) to post intervention (week 12) and follow-up (6 months after group intervention; month 9). The waiting control group can attend the group intervention at the end of all assessments. Participants allocated to the intervention group are expected to show improvement in their parenting and a reduction in child abuse potential. Maternal emotion regulation and mental distress are analyzed as secondary outcomes.

**Discussion:**

Mothers with BPD may need tailored help when reporting difficulties raising their children. The first disorder-specific parenting intervention has been developed to close this gap. ProChild is part of a large government-supported consortium, which aims to investigate different aspects of abuse and maltreatment in childhood and adolescence.

**Trial registration:**

ClinicalTrials.gov NCT04169048. Registered on Nov 19, 2019.

## Introduction

### Background

Borderline personality disorder (BPD) is found in approx. 1.7% of the general population, and 15–28% of patients in inpatient settings [1]. BPD is characterized by a pervasive instability in mood, self-image, and identity. In stressful situations, individuals with BPD frequently react with impulsive or self-harming behavior, easily lose their temper, or engage in self-damaging behavior (e.g., drinking, drug use, self-injury). Additionally, patients with BPD have difficulties engaging in and especially maintaining stable relationships, are hypersensitive to rejection, and often mistrust others. Even though evidence-based treatments for BPD are available [1, 2], and most of the patients recover over the life span [3], especially the years between ages 20 and 35 can be extremely challenging for individuals with BPD. Additionally, a severe and persistent impairment in social functioning has been observed [3]. Nevertheless, for this age typical normative developmental steps, such as getting married and starting a family, are common in BPD, too. This can lead to more stability and a sense of identity on the one hand—but on the other hand to even bigger challenges in managing every day’s life.

The borderline typical “stable instability” of interpersonal problems and emotion regulation [4] affects all daily interactions, including the parents’ relationship with their infant(s). Especially the first years of parenting are often a big challenge for parents with BPD. Factors such as sleep deprivation, changes in daily routines, and setting new priorities put the mothers under great pressure, reinforcing the borderline symptoms (e.g., impulsivity, self-harming behavior).

Considering that a healthy child development depends on the stability and dependability of the caregiver, it is crucial to offer mothers with BPD support in raising their children early on.

The primary goal of the presented randomized controlled trial (RCT) is to test the efficacy of a newly developed parenting group program for mothers with BPD ([5], English Version: [6]). The intervention is designed to promote positive parenting by teaching about the child’s primary needs, coping with parenting stress, emotion regulation, dealing with conflicts, and self-care. As prior research has focused on mothers with BPD and mothers mostly still are the caretakers early in life, the manual is conceptualized for mothers with BPD.

#### Mothers with BPD

An increasing number of studies point to the numerous difficulties mothers with BPD face (for an overview: [7–10]). Mothers with BPD often have difficulties in interpreting their offspring’s mental [11, 12], as well as emotional states [13], and thus have great difficulty responding sensitively to their infant’s needs [14]. A study investigating mother-infant dyads showed that mothers with high BPD traits perceived more negative emotions in their infants than could be objectified [15]. Furthermore, they reacted with more punitive and trivializing (invalidating) parenting behaviors than mothers with low BPD traits [15]. This behavior was mainly predicted by maternal emotion regulation difficulties [15]. In the communication with their children, mothers with BPD show increased hostility [16], more affective dysregulation, as well as more critical and intrusive behaviors, role confusion, and frightened/frightening behaviors than a non-clinical control group [17, 18].

Compared to non-clinical control groups, mothers with BPD feel less competent about parenting and perceive parenting as more stressful and less rewarding [14, 19, 20]. They rate their impact on their infants’ emotions and behavior weaker than a healthy control group does [13]. Additionally, they showed significantly more insecure, preoccupied and unresolved attachment patterns than a normative comparison group [21].

Parental BPD is also associated with a greater risk of child abuse [22, 23], whereas the effects of BPD on abuse potential are mediated by the severity of emotion regulation difficulties [23]. Abuse potential, in turn, is positively associated with child psychopathology [23]. Additionally, families with mothers diagnosed with BPD are often characterized by instability, low family cohesion, as well as frequent drug and alcohol abuse [24]. Further stressors like being a single parent, having low social support in the family, frequently changing partners and unstable households put mothers with BPD under additional personal stress, which may spill over into the parent–child dyad.

#### Children of mothers with BPD

Compared to children of healthy mothers, children of mothers with BPD have a higher risk for emotional and behavioral problems [7, 25]. This is also the case when compared to children of mothers with depressive disorders or cluster C personality disorders [26].

Already at an early stage, the offspring of mothers with BPD show signs of emotion dysregulation. Before the age of one, the infants were less responsive to their mothers [27] and expressed less positive phonation and more negative affect than infants of mothers with no psychopathology [28]. Furthermore, infants of mothers with BPD showed either too high or too low levels of fear expression [29].

Preschoolers and schoolchildren of mothers with BPD show more fear of abandonment [21] and parent–child role reversal [18]. They endure more maltreatment in an interaction task [30] compared to children of a healthy control group. In another study, mothers with BPD reported that their 4–7-year-old children had higher negative affectivity and lower effortful control compared to children of healthy mothers [31]. This was supported by teacher ratings of child behavior and child self-report (story completion task).

In adolescence, disruptive behavior, attention deficit/hyperactivity disorder (ADHD) and borderline symptoms appear to be more prevalent in children of mothers with BPD than in children of healthy mothers [32, 33]. Maternal borderline symptoms are associated with insecure, fearful attachment and poor self-perception in their youth offspring [34]. Mahan and colleagues [35] pointed at the link between maternal affective instability and adolescent’s affective instability, emphasizing the assumption of intergenerational transmission of BPD traits.

In sum, from infancy up to adolescence, children of mothers with BPD have a higher risk for emotional and behavioral problems than children of healthy mothers or children of mothers with other mental disorders such as depression.

Whereas the parental influence is strong in early childhood, peers and the social context gain relevance with age. Nevertheless, these early years are crucial for formative experiences and shape long-lasting ideations and schemes regarding one’s own needs, identity, and the formation of interpersonal relationships. To promote a healthy child development, the group intervention “Parenting Skills for Mothers with Borderline Personality Disorder” (5, English Version: 6) addresses mothers of young children between 6 months and 6 years. Consequently, dysfunctional parenting can be reduced or even prevented as early as possible.

### Objectives

The study *Parenting Skills for Mothers with BPD* is part of the consortium ProChild (“Preventing maltreatment and *pro*moting mental health in *child*ren of mothers with borderline personality disorder”), funded by the Federal Ministry of Education and Research (Bundesministerium für Bildung und Forschung; BMBF; 001KRI805A). ProChild aims across five subprojects to:Evaluate the group intervention described below in a randomized controlled trial (subproject 1, clinical registration: NCT04169048),Identify the specific characteristics and interactional patterns of children and their mothers with BPD compared to dyads with maternal anxiety or depressive disorders and dyads with healthy mothers (subprojects 2 and 3, non-intervention study registration: DRKS00020460), andAssess and derive recommendations for improved cooperation between childcare institutions, parents, and practitioners (subproject 5).

Subproject 4 analyzes epigenetic mechanisms in mothers and their children over time.

The current study protocol relates to the clinical trial (subproject 1). We will conduct and evaluate the first disorder-specific parenting intervention for mothers with BPD in a multi-center randomized controlled trial. The intervention is conceptualized as an add-on intervention to a completed or ongoing individual therapy focusing on the borderline symptomatology of the mother. Participation in the group program does not substitute individual psychotherapy. All participants must either have already completed or actually be in an individual treatment for their BPD.

The primary hypothesis is that the intervention has positive effects on parenting, and decreases child abuse potential directly after the intervention and at 6-month follow-up compared to a waiting control group. Secondary, it is hypothesized that the intervention reduces parental stress and enhances perceived parental competences. As well, an improvement in maternal emotion regulation and a reduction of mental distress is expected.

### Trial design

The trial is designed as a randomized, controlled, multi-center trial with two parallel groups. Randomization will be performed as clustered randomization with a 1:1 allocation by RedCap software for each study center separately.

## Methods: participants, interventions, and outcomes

### Study design, recruitment, and eligibility

Participants are recruited via three academic study centers in the German cities of Berlin, Bochum, and Bremen. Each study center cooperates with different in- and outpatient facilities, assisted living facilities, and individual therapists, through which participants with BPD are recruited. Most of these services are covered by the public health insurance, so that we expect the sample to be representative for mothers with BPD living in Germany. All participants will first be screened by a short telephone interview regarding their study eligibility (inclusion and exclusion criteria see below). When meeting the inclusion criteria, participants are invited to a face-to-face diagnostic interview (Structured Clinical Interview for DSM 5; SCID CV & SCID PD; German version: [36]; modules: mood disorders, psychotic symptoms, substance use disorders, anxiety disorders, posttraumatic stress disorder, BPD) to assess BPD symptoms and comorbid diagnosis as well as child-related psychopathology (subproject 2). Staff members who received a 2-day training and are supervised regularly conduct all diagnostic interviews. When still meeting inclusion criteria, participants obtain a personal link to complete several web-based questionnaires. Afterwards, they are invited to a first assessment with their child, where variables of subprojects 2, 3, and 4 are assessed. Participants are then randomized to the intervention or the waiting control group. All questionnaires and assessments are repeated post-interventional (week 12) and at follow-up 6 months later (month 9). After completing all assessment points, mothers randomized to the waiting control group are offered to participate in the parenting program (see also Table 1 SPIRIT schedule of enrollment, interventions, and assessments/participant timeline).

**Table 1 Tab1:** SPIRIT schedule of enrollment, interventions, and assessments

Timepoint	Study period																
	Enrolment		Allocation	Post-allocation													
				Intervention period													
			Basement (day 0)	Week 1	Week 2	Week 3	Week 4	Week 5	Week 6	Week 7	Week 8	Week 9	Week 10	Week 11	Week 12	Post-assessment (week 12)	Follow-up assessment (month 9)
Enrolment																	
Eligibility screen	x																
Informed consent	x																
Randomization BPD		x															
Intervention				x	x	x	x	x	x	x	x	x	x	x	x		
Assessments																	
Socio-demographics		x															
Diagnosis		x															
Primary outcomes			x													x	x
Secondary outcomes			x													x	x
Additional measures			x						x							x	x
Child protection routines		x		x	x	x	x	x	x	x	x	x	x	x	x		
Intervention related measures				x	x	x	x	x	x	x	x	x	x	x	x		

Participants must provide written, informed consent before participating in the face-to-face diagnostic interview. All assessments are rewarded monetary and children receive a small gift.

Inclusion criteria:Mothers with diagnosed BPD having children aged 6 months to 6 years (according to the age range addressed in the training “Parenting skills for mothers with BPD”)Mothers and their children must be in regular (weekly) contact or live togetherSufficient German language competenceMothers with BPD must have completed or must be currently receiving therapy for their BPD symptoms.

Exclusion criteria:Acute child endangermentAcute suicidalityAcute psychotic symptomsAcute alcohol or drug dependencyDiagnosed intellectual disability.

Trainers delivering the intervention should:Be femaleHave either kids on their ownOr be experienced in working with patients with BPDBe either licensed clinical psychotherapists or currently in training as clinical psychologists.

Having kids on their own helps trainers to understand the difficulties of participating mothers and to classify children’s behavior. As well, self-disclosure of the trainers regarding problems or doubts in child rearing facilitates mothers to open up.

Drop out criteria:Mothers who withdraw their participation after being included (after interview for eligibility)Mothers who cannot be reached within the defined time slots for post (week 12 + 2 months max.) and follow-up (month 9 + 2 months max.) assessments; if mothers miss out post assessment, they are still contacted for follow-up.

### Intervention

The manualized group-intervention “Parenting Skills for Mothers with Borderline Personality Disorder” [5, 6] is based on the concept of Dialectical Behavioral Therapy [37, 38]. DBT was developed to treat severe emotion dysregulation in BPD and focuses on the reduction of self-harming behavior, promotes mindfulness, and contains skills training to better cope with stress and high tension. BPD has proven to be effective in the treatment of BPD [2].

The group-intervention “Parenting Skills for Mothers with Borderline Personality Disorder” comprises 12 weekly 2 h-sessions covering the topics Psychoeducation, Mindfulness, Basic Needs of Children, Stress, Stress Management, Structure and Flexibility, Dealing with Conflicts, Dealing with Children’s and One’s Own Emotions, Physical Contact and Expression, Basic Assumptions about Parenting, and Self-Care. In the last session, all topics are summarized. Each session follows the same structure: mindfulness exercise, homework discussion, break, introduction into new topic using a practical exercise, homework for next session, take-home message. In-between sessions, participants are requested to practice newly gained techniques or knowledge in interaction with their children. Each session and the supporting material (i.e., information sheets and homework instructions) are described in detail in the manual.

#### Intervention—modifications

A Critical Incident Reporting System has been established. All serious adverse events (SAE) are documented. A consulting Data Safety Monitoring Committee (DSMC) is informed in cases of child or mother endangerment. The DSMC monitors all written reports of SAEs from the participating centers. Study exclusion only occurs in case of serious endangerment for the mother or child.

#### Intervention adherence

All group trainers receive a two-day training with the manual and role-play exercises by one of the manual’s authors. Frequent supervisions (every third session), video-based adherence checks, and adherence checklists after each session monitor adherence to the manual.

#### Intervention—concomitant care

As the intervention is conceptualized as an add-on parenting program, no restrictions are set regarding concomitant interventions as individual psychotherapy, skills training, or psychopharmacological medication.

### Outcomes

#### Primary outcome

Self-reported parenting is chosen as primary outcome as the intervention aims to reduce negative and enhance positive parenting. Additionally, child abuse potential is analyzed as primary outcome.

##### Primary outcome measures

Participants obtain a private link to complete primary outcome measures via web-based questionnaires at day 0 (before intervention), week 12 (directly after intervention), and month 9 (6 months after second assessment). Parenting strategies are assessed via the Brief Parenting Scale (German EFB-K; [39]) and the Alabama Parenting Questionnaire (German DEAPQ-EL-GS; [40]). Physical abuse potential is assessed using the Child Abuse Potential Inventory (CAPI; [41], German EBSK; [42]). Physical and psychological aggression towards the child is assessed via the Conflict Tactic Scale—Parent Child (CTS-PC; [43]) and the Child Neglect Index (CNI; [44]) filled out by the study staff and by the trainers in the intervention group after each session.

#### Secondary outcomes

In addition to direct effects on parenting and child abuse potential, changes in parental distress and perceived parental competencies are expected. Changes in borderline-specific psychopathologies (emotion regulation, mental distress, and borderline-specific thoughts and feelings) are also examined.

##### Secondary outcome measures

Participants rate their perceived parental competence and parental stress completing the Parenting Sense of Competence Scale (German EFB-K; 39) and the Parental Stress Index (German EBI; [45]).

Emotion regulation is assessed via the Difficulties in Emotion Regulation Scale (DERS; [46]), mental distress using the Brief Symptom Inventory (BSI; [47], German: [48]), and BPD-specific cognitions and emotions via the Questionnaire of Thoughts and Feelings (QTF; [49]).

All variables are assessed via web-based questionnaires on day 0 (before intervention), week 12 (after intervention), month 9 (6 months after second assessment).

#### Additional measures

To analyze potential control variables such as maternal trauma and conflicts in partnership, the Childhood Trauma Questionnaire (CTQ; [50], German version; [51]) at day 0 and the Conflict Tactic Scale for Partners (CTS-P; [52]) (day 0, week 12, and month 9) are applied. As an additional exploratory aspect, maternal mentalization is assessed using the Parental Reflective Functioning Questionnaire (PRFQ; [53]) (day 0, week 12, and month 9).

#### Additional outcomes in the intervention group only

After each session, trainers fill out the CNI (see above) and a form checking SAEs to check adverse events.

To assess unspecific intervention-related outcomes such as negative intervention effects and client satisfaction, a questionnaire assessing negative intervention outcomes (INEP; [54]) and the Client Satisfaction Questionnaire (CSQ-8; [55], German ZUF-8; [56]) are applied directly after the last session (week 12) in the intervention group only.

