### Power analysis and sample size

Because the primary hypothesis concerns the investigation of the effect of the intervention in contrast to the waiting control group, power calculation is based solely on a repeated measure, within-between ANOVA. We strive for a statistical power of 99%; multiple-comparison problems are considered according to Cramer et al. [57]. A conservative estimate of *r* = 0.5 is used for the correlation between repeated measures of the same outcome to ensure enough power for outcomes with relatively low stability over time. Using the software G-Power, these specifications lead to a required sample size of 110 patients (2*55 per group intervention/waiting group) to detect an interaction when Cohen’s *f* for the interactions of 2*3 ANOVA is assumed to be moderate at 0.20. Based on our pilot groups, we assume that 10% of participants assigned to the intervention will not start intervention after assignment. Dropout rates from psychotherapy trials for BPD range between 22.3% and 28.2% [58]. In conclusion, we expect a dropout rate from baseline to follow-up assessment of 25%. Therefore, we assess *n* = 178 mothers with BPD for eligibility (*n* = 160 start the trial, *n* = 140 at post assessment, *n* = 120 at follow-up).

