#### Statistical analyses of intervention effects

Analyses follow the intent-to-treat framework. In particular, we will use linear mixed effects models [59] with their advantages in the handling of missing and longitudinal data to analyze of our primary outcome measures. The respective statistical models will include fixed effects for time, intervention and the interaction of time and intervention as well as random effects for the participants.

Differences in the effectiveness of the intervention across three sites will be investigated. The factor site will be included in all statistical analyses concerning the primary and secondary outcome measures if there are substantive differences.

Additionally, the effect of concomitant interventions will be investigated.

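### INEP and ZUF-8 are tied to the last group session with no route for mothers who stop attending, so self-reported negative effects and satisfaction would probably come from completers only

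*Protocol article*

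**What the plan says.** The relevant text is in the protocol article, section Additional outcomes in the intervention group only. The two questionnaires serve this purpose: "To assess unspecific intervention-related outcomes such as negative intervention effects and client satisfaction". They "are applied directly after the last session (week 12) in the intervention group only". No other time point is given, and no mode of delivery.

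Table 1 (section Study design, recruitment, and eligibility) has one column for session week 12 and another for the week-12 post-assessment. Primary, secondary and additional measures are marked at post-assessment and month 9. The row "Intervention related measures" is marked in session weeks 1 to 12 and in neither later column.

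Harm is also recorded elsewhere. In the same section as INEP: "After each session, trainers fill out the CNI (see above) and a form checking SAEs to check adverse events". Under Intervention—modifications: "All serious adverse events (SAE) are documented", with review by the data safety monitoring committee.

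For efficacy, "Analyses follow the intent-to-treat framework". The listed drop-out criteria are withdrawal from the study and not being reachable in the assessment windows. Leaving the group early is not among them, and a mother who misses the post-assessment is still contacted for follow-up.

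**The concern.** A mother may attend a few sessions, feel worse because of the group, and stop coming. She remains in the trial and is still due the week-12 web questionnaires for the primary and secondary outcomes. Under the rule as written she is not at the last session, and nothing says that INEP or ZUF-8 reaches her by another path.

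The efficacy comparison would therefore keep her, while the one participant-reported instrument aimed at negative effects of the group would probably not. Being harmed or dissatisfied can itself be a reason to leave, so results restricted to completers are open to selection towards a favourable picture. This is the first evaluation of the program (Objectives), and the section Ancillary and post-trial care foresees wider establishment if it proves effective. Readers making that decision would want to know whom the tolerability and satisfaction figures describe.

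**Working it through.** **1. Does the rule point to the session or to the calendar week?**
- The INEP/ZUF-8 sentence names the last session and puts week 12 in parentheses after it.
- Table 1 separates session week 12 from the week-12 post-assessment and places intervention-related measures only under the sessions.
- The primary and secondary outcome sections name a web route for the week-12 assessment; the INEP/ZUF-8 sentence names none.

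Read together, collection at the session is the more natural reading. It is an inference: no sentence says that early leavers are left out.

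**2. The plan's own participant flow** (Power analysis and sample size)
- 178 × (1 − 0.10) = 160.2, stated as 160 starting.
- 160 × (1 − 0.25) = 120 at follow-up, as stated.
- 140 / 160 = 0.875, so 12.5% are lost by post-assessment. That is about 10 of 80 in the intervention arm, assuming equal arms and equal losses.

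The flow reproduces. These are losses to assessment; the number leaving the group early is not given anywhere.

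**3. Illustration of the possible bias**

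All-starter rate = (1 − s) × p_c + s × p_l, where s is the share of starters not asked, p_c the rate among completers and p_l the rate among leavers. A completers-only report shows p_c.

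Assumptions: s = 0.125 (the assessment loss, as a stand-in) and p_c = 0.10 (not in the documents).

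| Leavers reporting a negative effect | All-starter rate | Completers-only report is |
|---|---|---|
| 5% | 0.875 × 0.10 + 0.125 × 0.05 = 9.4% | 0.6 points too high |
| 10% | 0.875 × 0.10 + 0.125 × 0.10 = 10.0% | unbiased |
| 20% | 0.875 × 0.10 + 0.125 × 0.20 = 11.3% | 1.3 points too low |
| 40% | 0.875 × 0.10 + 0.125 × 0.40 = 13.8% | 3.8 points too low |

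If s were 0.25 instead, leavers at 20% give 0.75 × 0.10 + 0.25 × 0.20 = 12.5%, and leavers at 40% give 0.75 × 0.10 + 0.25 × 0.40 = 17.5%. Direction and size both depend on quantities that the documents do not supply.

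**4. Do the other harm channels fill the gap?**
- The trainers' neglect index and serious-adverse-event form are completed by trainers after each session, so they cover an early leaver only while she attends.
- Serious-event documentation and committee review concern serious events and endangerment.
- The symptom and stress questionnaires in both arms can show worsening, but they do not ask whether the group caused it.

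None of these records self-reported negative effects attributed to the group.

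**The case against.** The strongest case against runs as follows.

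- **The text does not exclude early leavers.** It names the intervention group, not attenders, and the primary outcomes are timed in similar words. The Table 1 row also covers the per-session forms, so it does not settle who receives INEP. This stands in part. A reader might conclude that the protocol excludes mothers who stop early, but it is silent on them. The separate Table 1 columns and the missing web route make exclusion likely, not certain.
- **The detail may be in a standard operating procedure.** The Auditing section says that all processes are set out in such procedures. That is possible. The article nevertheless states a time point, and the point here is the time point it states.
- **Harm is not shown to be understated.** This stands. A reader might take understatement as established, but with equal rates the bias is zero, and with lower rates among leavers it reverses. Mothers who worsen also remain in the randomized comparison if they answer the questionnaires.
- **The dropout literature does not measure leaving this group.** This stands too. The protocol notes that "Dropout rates from psychotherapy trials for BPD range between 22.3% and 28.2" per cent. Applying that range here, with 10% and 40% as the completer and leaver rates, would give 16.7% to 18.5%. The protocol uses the range to support its 25% loss from baseline to follow-up assessment, so those larger figures are not supported.
- **These are additional outcomes.** This is correct. No hypothesis or sample size rests on them, and the article ties roll-out to effectiveness.

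**Conclusion.** The point holds in a limited form. The protocol ties INEP and ZUF-8 to the last session, not to the week-12 post-assessment, and describes no route for mothers who stop attending. Self-reported negative effects and satisfaction would therefore probably come from completers only, and negative effects may be understated.

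Under the stand-in assumptions, a reported 10% would correspond to between 10% and 13.8% among all starters if leavers report negative effects as often as completers or up to four times as often. It would correspond to less than 10% if they report them less often. These figures show how the bias behaves and are not estimates for this trial. The change is worth making because it is cheap and because answers from mothers who have left are hard to recover later. Primary and secondary analyses are unaffected.

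**What to change.** Change the INEP/ZUF-8 sentence and the corresponding Table 1 row so that both forms go out with the week-12 web questionnaire link to every intervention-arm mother who attended at least one session, whether or not she attended the last one. Report the results with session starters as denominator, give the response rate, and show completers and early leavers separately.

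The cost is two short questionnaires on a link these mothers are already due to receive, plus a change of wording in the protocol and operating procedures. Some early leavers will not respond, and those who miss the week-12 assessment altogether will still be missed, which is why the response rate must be shown. The post-assessment window runs up to two months past week 12, so some answers may come later than directly after the last session. The results may look slightly less favourable.
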